|  | 
which at least includes the start date, end date, severity, relationship with the investigational drug, outcome, duration and other information.
 
Safety variables (vital signs, laboratory data, ECG, etc.) will be grouped and summarized according to the time points specified in the protocol. Concomitant medications will be classified and summarized by group. All other safety data (physical examination, blood pregnancy, PHQ-9 score, etc.) will be reflected in the form of a list. The changes of laboratory examination results, ECG and physical examination before and after treatment will be statistically described in the form of a cross table, and the list of subjects with abnormal clinical significance after treatment will be listed.
 
The summarized table will present the number and percentage of events. In addition, the Treatment Emergent Adverse Events (TEAEs) will be summarized according to the severity and the relationship with the investigational drug. TEAE is defined as adverse events after the use of investigational drugs, and the analysis of adverse events will be based on TEAE. Serious adverse events will also be summarized and listed separately.
 
For the same subject, if an adverse event occurs multiple times, it will be counted as one case when calculating the incidence of adverse events.
 
The adverse events leading to the early termination of the study medication will be described.
 
Immunogenicity evaluation index: the titer of ADA and NAB in serum according to groups, and the number and incidence of subjects with positive ADA and NAB will be described.
 
Heart rate, blood amylase and lipase will also be further analyzed using the covariance model (ANCOVA).
 
The dose-dependent assessment of safety and tolerability is based on five GZR18 injection study groups with four dose groups and two administration methods, and compared with the placebo control group to summarize the adverse events in each group.
 
PK analysis
 
Based on PKPs, Phoenix WinNonlin 8.3 or above is used for PK analysis. The list and descriptive statistics of the investigational drugs are carried out, and the average drug concentration-time curves of individual and group are drawn respectively. The PK parameters are calculated by non atrioventricular model according to the actual blood sampling time, and the parameters are summarized by descriptive statistics. The main pharmacokinetic parameters are summarized by the number of subjects, arithmetic mean, standard deviation, coefficient of variation (CV),
 |
|--|--------------------------------------------------------------------------------------------------------------------------------------------------------------------------------------------------------------------------------------------------------------------------------------------------------------------------------------------------------------------------------------------------------------------------------------------------------------------------------------------------------------------------------------------------------------------------------------------------------------------------------------------------------------------------------------------------------------------------------------------------------------------------------------------------------------------------------------------------------------------------------------------------------------------------------------------------------------------------------------------------------------------------------------------------------------------------------------------------------------------------------------------------------------------------------------------------------------------------------------------------------------------------------------------------------------------------------------------------------------------------------------------------------------------------------------------------------------------------------------------------------------------------------------------------------------------------------------------------------------------------------------------------------------------------------------------------------------------------------------------------------------------------------------------------------------------------------------------------------------------------------------------------------------------------------------------------------------------------------------------------------------------------------------------------------------------------------------------------------------------------------------------------------------------------------------------------------------------------------------------------------------------------------------------------------------------------------------------------------------------------------------------------------------------------------------------------------------------------------------------------------------------------------------------------------------------------------------------------------------------------------------------------------------------------------------------|

|  |                                                                                                                                                                                                                                                                                                                                                                                      |
|--|--------------------------------------------------------------------------------------------------------------------------------------------------------------------------------------------------------------------------------------------------------------------------------------------------------------------------------------------------------------------------------------|
|  | 
median, minimum, maximum, geometric mean and geometric coefficient of variation. Power model is used to explore the linear characteristics of pharmacokinetic parameters and dose when the data are sufficient.
 
Statistical programming
 
Statistical programming will be completed with SAS 9.4 version or above, Phoenix WinNonlin 8.3 version or above.
 |
|--|--------------------------------------------------------------------------------------------------------------------------------------------------------------------------------------------------------------------------------------------------------------------------------------------------------------------------------------------------------------------------------------|

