#### Analysis sets

**Full Analysis Set (FAS):** FAS includes all randomized subjects who received at least one dose of the investigational drug. The data set is the main analysis set of demographic data, baseline indicators, medical history and curative effect.

**Per Protocol Set (PPS):** PPS is a subset of FAS, which includes subjects who met all inclusion criteria, did not meet exclusion criteria, had primary endpoint efficacy indicators and did not have other major protocol deviations. The data set is used for the supportive analysis of efficacy.

**Safety Set (SS):** SS includes all randomized subjects who received at least one dose of investigational drug and had at least one safety evaluation. This data set is used for statistical analysis of safety indicators.

**PK Concentration Set (PKCS):** PKCS includes all randomized subjects who received at least one dose of investigational drug and had at least one measured plasma concentration of the investigational drug available after medication.

**PK Parameter Set (PKPS):** PKPS includes all randomized subjects who received at least one dose of the investigational drug and had at least one valid PK parameter of the investigational drug during the study.

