|                        | 
 
 Alternative hypothesis	<math>H_1: \mu_T - \mu_C < 0</math>	
 
 
<math>\mu_T</math> is the mean percentage change of body weight from baseline in the first to fifth dose groups after 30 weeks of GZR18 treatment (<math>\mu_T</math> includes <math>\mu_{T1}</math>, <math>\mu_{T2}</math>, <math>\mu_{T3}</math>, <math>\mu_{T4}</math> and <math>\mu_{T5}</math>, which corresponds to GZR18 s.c. 12 mg once every two weeks, GZR18 s.c. 18 mg once every two weeks, GZR18 s.c. 24 mg once every two weeks, GZR18 s.c. 48 mg once every two weeks and GZR18 s.c. 24 mg once-weekly respectively), <math>\mu_C</math> is the mean percentage change of body weight from baseline in the first to fifth dose groups after 30 weeks of placebo treatment. <math>\alpha</math> is significance level (Type I error rate).
 
Primary endpoint analysis: the percentage of body weight change (%) from baseline at week 30 will be taken as the primary endpoint, which will be analyzed based on the covariance model (ANCOVA), where, with baseline body weight as the covariate and group as the fixed effect, and the change from baseline is the dependent variable. The following indicators will be then calculated: the least-squares mean (LSMean) and its two-sided 95% CI of the percentage of the change from baseline in both groups, as well as the LSMean difference between the treatment and control groups and its two-sided 95% CI.
 
Secondary endpoint analysis: The continuity variables will be analyzed by the same method as the primary endpoint analysis. The number of cases reaching the target end point and the rate of reaching the target and its two-sided 95% CI will be counted in the analysis of the proportion between the two groups. At the same time, the rate difference between the two groups (the investigational drug group and the placebo group) and its two-sided 95% CI will be calculated. The rate of reaching the target and the two-sided 95% CI of the rate difference between the two groups will be calculated by the Clopper-Pearson Exact method.
 
Sensitivity analysis
 
Sensitivity analysis of main efficacy indicators.
 
 
1. The Mixed Model Repeated Measures (MMRM) method will be used to incorporate all time points from baseline to week 30 into the Linear Mixed model (LMM) as a supporting analysis to compare the efficacy differences between the treatment group and the placebo group.
 
2. Consistent with the primary endpoint analysis method, some specific populations will be excluded for comparison of efficacy between groups.
 
 
Statistical analysis of safety endpoints
 
Adverse events will be summarized for each treatment group using Medical Dictionary for Regulatory Activities (MedDRA) according to System Organ Class (SOC) and Preferred term (PT). All adverse events are presented in the form of a list,
 | Alternative hypothesis | $H_1: \mu_T - \mu_C < 0$ |

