#### Other

All efficacy analyses are performed primarily in FAS. To verify the robustness of the efficacy results, the primary efficacy variable is also analyzed for PPS. Safety analysis is conducted in SS.

All efficacy analyses are based on randomized treatment assignment, Safe analysis based on actual groups. Subjects receiving incorrect treatment are evaluated during a blinded Data Evaluation Meeting (DEM) to assess the potential impact of such cases and any special analytical considerations.

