## **9.4 Scheduled efficacy analysis**

hypothesis-testing:

|                        |                                                                                   |
|------------------------|-----------------------------------------------------------------------------------|
|                        | Percentage change in body weight from baseline to W30 (one-sided $\alpha=0.025$ ) |
| Null hypothesis        | $H_0: \mu_T - \mu_C \geq 0$                                                       |
| Alternative hypothesis | $H_1: \mu_T - \mu_C < 0$                                                          |

$\mu_T$  is the mean percentage change of body weight from baseline in the first to fifth dose groups after 30 weeks of GZR18 treatment ( $\mu_T$  includes  $\mu_{T1}$ ,  $\mu_{T2}$ ,  $\mu_{T3}$ ,  $\mu_{T4}$  and  $\mu_{T5}$ , which corresponds to GZR18 s.c. 12 mg once every two weeks, GZR18 s.c. 18 mg once every two weeks, GZR18 s.c. 24 mg once every two weeks, GZR18 s.c. 48 mg once every two weeks and GZR18 s.c. 24 mg once-weekly respectively),  $\mu_C$  is the mean percentage change of body weight from baseline in the first to fifth dose groups after 30 weeks of placebo treatment.  $\alpha$  is significance level (Type I error rate).

Based on FAS, conduct effectiveness analysis on efficacy indicators. PPS as a supportive analysis result.

Primary endpoint analysis: the percentage of body weight change (%) from baseline at week 30 will be taken as the primary endpoint, which will be analyzed based on the covariance model (ANCOVA), where, with baseline body weight as the covariate and group as the fixed effect, and the change from baseline is the dependent variable. The following indicators will be then calculated: the least-squares mean (LSMean) and its two-sided 95% CI of the percentage of the change from baseline in both groups, as well as the LSMean difference between the treatment and control groups and its two-sided 95% CI.

Secondary endpoint analysis: The continuity variables will be analyzed by the same method as the primary endpoint analysis. The number of cases reaching the target end point

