### **Sensitivity analysis**

Sensitivity analysis of main efficacy indicators. The Mixed Model Repeated Measures (MMRM) method will be used to incorporate all time points from baseline to week 30 into the Linear Mixed model (LMM) as a supporting analysis to compare the efficacy differences between the treatment group and the placebo group. Consistent with the primary endpoint analysis method, some specific populations are excluded for comparison of efficacy between groups.

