### **9.8 Determination of sample size**

Based on the study results of similar drugs and the non-clinical data of GZR18 and the existing clinical human pharmacodynamic data of GZR18, it is estimated that the difference of the percentage of body weight change from baseline at W30 between GZR 18 and placebo group is 11% (GZR18 weight loss of 13%, placebo group weight loss of 2%), the combined standard deviation is 10%, the degree of grasp is 0.8, one-side  $\alpha$  0.025, GZR18 group: placebo group: 4:1, then the calculated sample size is 40 subjects for GZR18 investigational drug and 10 subjects for placebo. Considering the 20% dropout rate, 52 subjects receive GZR18 investigational drug and 13 subjects receive placebo actually. There are five dose groups of GZR18, including the 12 mg/18 mg/24 mg once every two weeks' group and the 24 mg (18 mg) once-weekly group, with 52 subjects in each investigational drug group and 13 subjects in the placebo group; The subjects in the 48 mg once every two weeks' group may not titrate 48 mg due to intolerance to AE, so the number of subjects in the GZR18 group is increased to 78 (65 subjects for the GZR18 investigational drug and 13 people for the placebo group). The total sample size is 338 subjects.

The number of people to be enrolled will be determined based on the assessment of data from nonclinical studies of GZR18 and some data from the clinical trial of GZR18, as well as the number of Phase II clinical trials of similar drugs under development or already marketed, and information considered sufficient by the investigator and sponsor to achieve the trial objectives.

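### None of the named robustness checks keeps dropouts and lets those who left on drug lose benefit, and one of them removes randomised subjects by a rule that is not fixed

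*Protocol*

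**What the plan says.** The primary analysis is an ANCOVA of percentage weight change at week 30 in the full analysis set (Protocol 9.4). Section 9.7 uses the last efficacy value of a subject who stops early, which is in effect last observation carried forward.

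Three checks are named around it:

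- **Per-protocol set.** Section 9.1 (Other) gives its purpose: "To verify the robustness of the efficacy results, the primary efficacy variable is also analyzed for PPS". Its definition admits only subjects who "had primary endpoint efficacy indicators and did not have other major protocol deviations".
- **MMRM.** It uses all visits to week 30 (1.1 Summary, Sensitivity analysis item 1, and 9.4).
- **Restricted rerun.** The Summary (item 2) says "Consistent with the primary endpoint analysis method, some specific populations will be excluded for comparison of efficacy between groups". Section 9.4 says that "some specific populations are excluded for comparison of efficacy between groups". Neither place names the populations.

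Section 9.8 plans for 20% dropout. Section 6.1 (Dose adjustment standards) has subjects who are intolerant at 12 mg or below leave the trial itself, and it names gastrointestinal intolerance as the main adverse reaction of the class.

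**The concern.** A robustness check is useful if it varies the assumption most likely to be wrong. Here that assumption concerns dropouts. Withdrawal for intolerance is written into the design and should fall mainly on GZR18. The protocol itself makes loss of benefit after stopping plausible: section 2.1 describes the body's tendency to regain weight, and section 3.2 makes weight at week 33, after drug withdrawal, a secondary endpoint.

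None of the three checks addresses this. The per-protocol set, read as requiring a week-30 value, drops those who left. The MMRM predicts their course from subjects in the same arm with a similar weight history. The restricted rerun keeps the primary method and changes only the population, so it varies no missing-data assumption. It also takes subjects out of a randomised comparison by a rule that is still open. Section 9.6 has analysis populations settled at a data meeting before unblinding, but by then the outcome data have been collected.

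What is at stake is the effect size that a phase II trial hands to later development, and whether it may be called robust.

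**Working it through.** **Inputs from section 9.8.** Mean week-30 change is -13% on GZR18 and -2% on placebo. "the combined standard deviation is 10"%. Power is 0.8, one-sided alpha 0.025, allocation 4:1, dropout 20%, with 52 + 13 randomised per dose group (65 + 13 for 48 mg).

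**The plan's own figures.** Placebo n = 1.25 × (10 × (1.960 + 0.842) / 11)² = 8.1, hence 9 + 36. The stated 40 + 10 is recovered only if 0.025 is read as two-sided, so it errs on the large side and does not affect this point. Dropout: 10 / 0.8 = 12.5, so 13, and 4 × 13 = 52. Total: 4 × 65 + 78 = 338.

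**Per-protocol set and MMRM.** Taking the plan's means as those of subjects who stay, both target -13 - (-2) = -11 points.

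**GZR18 dropouts end at the placebo mean, all randomised subjects counted.** With dropout fraction d on GZR18, the difference is (1 - d)(-13) + d(-2) - (-2):

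- d = 20% (plan): -10.4 - 0.4 + 2 = -8.8, which is 2.2 points below 11.
- d = 10% (assumed): -9.9.
- d = 30% (assumed): -7.7.

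If dropouts end at -5 or -8 instead (assumed), d = 20% gives -9.4 or -10.0.

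**Primary analysis with the last value.** Assume a straight-line path to week 30 and 20% dropout in both arms at week w. Each arm mean m becomes 0.8m + 0.2m × w/30.

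- w = 8: -11.09 - (-1.71) = -9.4.
- w = 20: -12.13 - (-1.87) = -10.3.

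**Simulation.** 20,000 subjects per arm, linear mean paths, 20% random dropout per arm. A within-arm sequential regression stands in for the MMRM.

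| GZR18 dropouts | All randomised | Last value | Completers | Missing at random |
|---|---|---|---|---|
| leave W8, end at -2 | -8.97 | -9.52 | -11.13 | -11.12 |
| leave W20, end at -2 | -8.83 | -10.25 | -10.98 | -10.96 |
| leave W20, keep half their loss | -9.47 | -10.47 | -11.18 | -11.23 |

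In each row the last-value primary overstates the effect, and the completer and missing-at-random results lie further from the all-randomised figure than the primary does.

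**Significance.** For 52 against 13 with SD 10, the smallest significant difference is 1.96 × 10 × √(1/52 + 1/13) = 6.1 points. The lowest figure above, 7.7, still exceeds it.

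**The case against.** A reader might infer that every planned check either removes dropouts or treats them as if they had stayed, so that no check could ever reveal an overstated effect. The documents do not support that, for three reasons.

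- The restricted rerun names no population, so the text does not say that dropouts are removed. Any who remain are handled by the last-value rule in section 9.7.
- The MMRM conditions on arm and on each subject's own weights, which is weaker than assuming that dropouts do as well as those who stayed.
- The MMRM can fall below the primary. With 30% placebo dropout at week 8 and none on GZR18, the last-value placebo mean is 0.7(-2) + 0.3(-2)(8/30) = -1.56. The primary then gives -11.44 and the MMRM about -11.0.

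A reader might also infer that the restricted rerun inflates the effect. That cannot be claimed while the excluded set is unknown. One possible set visible in the protocol is the weekly-dose subjects who declined the move from 18 mg to 24 mg. They choose without knowing whether they receive drug or placebo, so no direction of bias follows.

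The primary rule also gives early leavers little weight loss. If they in fact held -8, the all-randomised difference at 20% dropout would be 10.0, and a primary of 9.4 (dropout at week 8) would be too low.

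Sections 9.1 and 9.4 already call the per-protocol analysis supportive, and a SAP not seen here may name the populations or add a stress test.

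These objections remove the absolute claims. They leave two facts in the protocol: section 9.1 assigns robustness to a set that excludes subjects without the endpoint, and no named check gives drug dropouts a less favourable outcome.

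**Conclusion.** The point holds in limited form. The named checks include none that keeps dropouts and lets those who left on GZR18 lose benefit, and item 2 excludes randomised subjects by an unfixed rule.

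On the plan's means and 20% dropout, the per-protocol and MMRM targets exceed the all-randomised difference by 2.2 points (11 against 8.8) if GZR18 dropouts end at the placebo mean. The gap is 1.1 points at 10% dropout and 3.3 at 30%. A primary of about 9.4 to 10.3 would then be overstated, yet would look cautious beside checks near 11.

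This rests on assumed dropout timing, on assumed end weights, and on the plan's means describing subjects who stay. It concerns the size of the estimate. Significance is unlikely to change.

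**What to change.** In the Summary (Sensitivity analysis, item 2) and the matching text in 9.4, replace the undefined exclusion with one named sensitivity analysis on all subjects in the full analysis set:

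- Impute missing week-30 weight by multiple imputation.
- Impute GZR18 dropouts from the same placebo group that serves as comparator in the primary ANCOVA (jump to reference), and placebo dropouts within placebo.
- Fit the same ANCOVA and combine by Rubin's rules.

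Keep the MMRM. In section 9.1 (Other), do not present the per-protocol rerun as evidence of robustness to dropout.

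The change needs revised wording and one extra programmed analysis, with no new data or subjects. The price is one sensitivity figure that will probably be less favourable.

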## 1.2 Study flowchart

| Assessment                                                                                  | Screening | Baseline | Study visit |     |     |     |     |     |     |      |      |      |      |      |      |      |      | Safety follow-up | Early termination |
|---------------------------------------------------------------------------------------------|-----------|----------|-------------|-----|-----|-----|-----|-----|-----|------|------|------|------|------|------|------|------|------------------|-------------------|
| Visit                                                                                       | V1        | V2       | V3          | V4  | V5  | V6  | V7  | V8  | V9  | V10  | V11  | V12  | V13  | V14  | V15  | V16  | V17  | V18              | ET                |
| Week(W)                                                                                     | W-1       | W0       | W2          | W4  | W6  | W8  | W10 | W12 | W14 | W16  | W18  | W20  | W22  | W24  | W26  | W28  | W30  | W33              |                   |
| Day(D)                                                                                      | D-7~D-1   | D0       | D14         | D28 | D42 | D56 | D70 | D84 | D98 | D112 | D126 | D140 | D154 | D168 | D182 | D196 | D210 | D231             |                   |
| Time window(days)                                                                           |           |          | ±2          | ±2  | ±2  | ±2  | ±2  | ±2  | ±2  | ±2   | ±2   | ±2   | ±2   | ±2   | ±2   | ±2   | ±2   | ±3               |                   |
| Signing of ICF                                                                              | X         |          |             |     |     |     |     |     |     |      |      |      |      |      |      |      |      |                  |                   |
| Inclusion and exclusion criteria                                                            | X         | X        |             |     |     |     |     |     |     |      |      |      |      |      |      |      |      |                  |                   |
| Demographics                                                                    | X         |          |             |     |     |     |     |     |     |      |      |      |      |      |      |      |      |                  |                   |
| Past history and comorbidities                                                  | X         |          |             |     |     |     |     |     |     |      |      |      |      |      |      |      |      |                  |                   |
| Concomitant treatment/medication                                                            | X         | X        | X           | X   | X   | X   | X   | X   | X   | X    | X    | X    | X    | X    | X    | X    | X    | X                | X                 |
| Immunoserologic panel test                                                      | X         |          |             |     |     |     |     |     |     |      |      |      |      |      |      |      |      |                  |                   |
| Pregnancy test                                                                  | X         | X        |             | X   |     | X   |     | X   |     | X    |      | X    |      | X    |      |      | X    | X                | X                 |
| Chest X-ray (anteroposterior and lateral view) or lung CT                       | X         |          |             |     |     |     |     |     |     |      |      |      |      |      |      |      |      |                  |                   |
| Hepatobiliary, pancreatic, splenic and urinary system color Doppler ultrasound  | X         |          |             |     |     |     |     |     |     |      |      |      |      |      |      |      |      |                  |                   |
| OGTT                                                                                        | X         |          |             |     |     |     |     |     |     |      |      |      |      |      |      |      |      |                  |                   |

| Assessment                                                                            | Screening | Baseline | Study visit |     |     |     |     |     |     |      |      |      |      |      |      |      |      | Safety follow-up | Early termination |
|---------------------------------------------------------------------------------------|-----------|----------|-------------|-----|-----|-----|-----|-----|-----|------|------|------|------|------|------|------|------|------------------|-------------------|
| Visit                                                                                 | V1        | V2       | V3          | V4  | V5  | V6  | V7  | V8  | V9  | V10  | V11  | V12  | V13  | V14  | V15  | V16  | V17  | V18              | ET                |
| Week(W)                                                                               | W-1       | W0       | W2          | W4  | W6  | W8  | W10 | W12 | W14 | W16  | W18  | W20  | W22  | W24  | W26  | W28  | W30  | W33              |                   |
| Day(D)                                                                                | D-7~D-1   | D0       | D14         | D28 | D42 | D56 | D70 | D84 | D98 | D112 | D126 | D140 | D154 | D168 | D182 | D196 | D210 | D231             |                   |
| Time window(days)                                                                     |           |          | ±2          | ±2  | ±2  | ±2  | ±2  | ±2  | ±2  | ±2   | ±2   | ±2   | ±2   | ±2   | ±2   | ±2   | ±2   | ±3               |                   |
| Drug abuse screening (urine)                                              | X         | X        |             |     |     |     |     |     |     |      |      |      |      |      |      |      |      |                  |                   |
| Blood biochemistry (including blood lipids), hematology, and coagulation  | X         |          |             |     |     | X   |     | X   |     | X    |      | X    |      | X    |      |      | X    | X                | X                 |
| Amylase and lipase                                                                    | X         |          |             |     |     | X   |     | X   |     | X    |      | X    |      | X    |      |      | X    | X                | X                 |
| TSH/FT3/FT4                                                                           | X         |          |             |     |     | X   |     | X   |     | X    |      | X    |      | X    |      |      | X    | X                | X                 |
| Calcitonin                                                                            | X         |          |             |     |     | X   |     | X   |     | X    |      | X    |      | X    |      |      | X    | X                | X                 |
| Urinalysis                                                                | X         |          |             |     |     | X   |     | X   |     | X    |      | X    |      | X    |      |      | X    | X                | X                 |
| ECG                                                                       | X         |          |             |     |     | X   |     | X   |     | X    |      | X    |      | X    |      |      | X    | X                | X                 |
| Physical examinations                                                     | X         |          |             |     |     | X   |     | X   |     | X    |      | X    |      | X    |      |      | X    | X                | X                 |
| Vital signs                                                              | X         | X        | X           | X   | X   | X   | X   | X   | X   | X    | X    | X    | X    | X    | X    | X    | X    | X                | X                 |
| Fundus examination                                                                    | X         |          |             |     |     |     |     |     |     | X    |      |      |      |      |      |      | X    | X                | X                 |
| Injection site observation                                               |           | X        | X           | X   | X   | X   | X   | X   | X   | X    | X    | X    | X    | X    | X    | X    | X    | X                | X                 |
| Immunogenicity blood sampling                                            |           | X        |             | nab |     |     |     |     |     | X    |      |      |      |      |      |      | X    | X                | X                 |
| PHQ-9 scores                                                                          | X         |          |             |     |     |     |     | X   |     |      |      |      |      | X    |      |      |      | X                | X                 |
| Evaluation of Columbia-suicide severity rating scale                                  | X         |          |             |     |     |     |     | X   |     |      |      |      |      | X    |      |      |      | X                | X                 |
| Adverse event                                                                         |           | X        | X           | X   | X   | X   | X   | X   | X   | X    | X    | X    | X    | X    | X    | X    | X    | X                | X                 |

| Assessment                                                          | Screening | Baseline | Study visit |     |                |     |                |     |                |      |                |                |      |                |      |                |      | Safety follow-up | Early termination |
|---------------------------------------------------------------------|-----------|----------|-------------|-----|----------------|-----|----------------|-----|----------------|------|----------------|----------------|------|----------------|------|----------------|------|------------------|-------------------|
| Visit                                                               | V1        | V2       | V3          | V4  | V5             | V6  | V7             | V8  | V9             | V10  | V11            | V12            | V13  | V14            | V15  | V16            | V17  | V18              | ET                |
| Week(W)                                                             | W-1       | W0       | W2          | W4  | W6             | W8  | W10            | W12 | W14            | W16  | W18            | W20            | W22  | W24            | W26  | W28            | W30  | W33              |                   |
| Day(D)                                                              | D-7~D-1   | D0       | D14         | D28 | D42            | D56 | D70            | D84 | D98            | D112 | D126           | D140           | D154 | D168           | D182 | D196           | D210 | D231             |                   |
| Time window(days)                                                   |           |          | ±2          | ±2  | ±2             | ±2  | ±2             | ±2  | ±2             | ±2   | ±2             | ±2             | ±2   | ±2             | ±2   | ±2             | ±2   | ±3               |                   |
| Body measurements                                      | X         | X        | X           | X   | X              | X   | X              | X   | X              | X    | X              | X              | X    | X              | X    | X              | X    | X                | X                 |
| Fasting blood glucose, insulin                         | X         |          |             |     |                |     |                |     |                |      |                |                |      |                |      |                | X    |                  |                   |
| Glycosylated hemoglobin                                             | X         |          |             |     |                |     |                |     |                |      |                |                |      |                |      |                | X    |                  |                   |
| IWQoL-Lite-CT questionnaire                                         |           | X        |             |     |                |     |                | X   |                |      |                |                |      | X              |      |                | X    |                  | X                 |
| SF-36 questionnaire                                                 |           | X        |             |     |                |     |                | X   |                |      |                |                |      | X              |      |                | X    |                  | X                 |
| PK blood sampling                                      |           | X        |             |     | X a |     | X b |     | X c |      | X d | X e |      | X f | X    | X g | X    |                  |                   |
| Randomization                                                       |           | X        |             |     |                |     |                |     |                |      |                |                |      |                |      |                |      |                  |                   |
| Hospital Administration                                |           | X        | X           | X   | X              | X   | X              | X   | X              | X    | X              | X              | X    | X              | X    | X              |      |                  |                   |
| Training and distribution of injection pen             |           | X        |             |     |                |     |                |     |                |      |                |                |      |                |      |                |      |                  |                   |
| Dispensing of drugs (only once-weekly administration)  |           | X        | X           | X   | X              | X   | X              | X   | X              | X    | X              | X              | X    | X              | X    |                |      |                  |                   |
| Recovery of drugs (only once-weekly administration)    |           |          | X           | X   | X              | X   | X              | X   | X              | X    | X              | X              | X    | X              | X    | X              |      |                  |                   |
| Evaluation of drug use compliance outside hospital (only            |           |          | X           | X   | X              | X   | X              | X   | X              | X    | X              | X              | X    | X              | X    | X              |      |                  |                   |

| Assessment                                | Screening | Baseline | Study visit |     |     |     |     |     |     |      |      |      |      |      |      |      |      | Safety follow-up | Early termination |
|-------------------------------------------|-----------|----------|-------------|-----|-----|-----|-----|-----|-----|------|------|------|------|------|------|------|------|------------------|-------------------|
| Visit                                     | V1        | V2       | V3          | V4  | V5  | V6  | V7  | V8  | V9  | V10  | V11  | V12  | V13  | V14  | V15  | V16  | V17  | V18              | ET                |
| Week(W)                                   | W-1       | W0       | W2          | W4  | W6  | W8  | W10 | W12 | W14 | W16  | W18  | W20  | W22  | W24  | W26  | W28  | W30  | W33              |                   |
| Day(D)                                    | D-7~D-1   | D0       | D14         | D28 | D42 | D56 | D70 | D84 | D98 | D112 | D126 | D140 | D154 | D168 | D182 | D196 | D210 | D231             |                   |
